### 3.6. Selected Lifestyle Factors

The participants’ levels of physical activity will be assessed using the International Physical Activity Questionnaire (IPAQ), validated by Biernat et al. [39]. The Polish version quantifies physical activity in metabolic equivalent of task (MET)-min/week units, which allows the respondents to be easily classified into one of three categories of activity: insufficient (below 600), sufficient (600–3000), or high (above 3000 MET-min/week). The questionnaire comprises two parts: The first includes six brief questions (with Yes/No responses), designed to verify whether the preceding seven days were representative of the participant’s typical level of physical activity. In the second part, participants answer seven questions related to physical activities at both intense and moderate levels, as well as all walking and sitting [39].

Self-reported data on health status, sleep duration, and smoking status will be collected using the KomPAN questionnaire [36]. Additionally, all participants will be queried about ongoing medical care, medications, and dietary supplements and herbs, along with an assessment of their stress levels.

### 3.7. Quality of Life

The quality of life of the participants will be assessed using the Quality of Life Questionnaire for Patients with Thyroid Diseases (ThyPROpl).

ThyPROpl is a thyroid-specific questionnaire validated for the Polish population by Sawicka-Gutaj et al. [38]. The questionnaire comprises 85 questions grouped into 13 scales measuring aspects of quality of life relevant to thyroid patients. The 13-point scale includes questions on (1) symptoms, (2) feeling tired, (3) energy, (4) memory and concentration, (5) nervousness and tension, (6) mental well-being, (7) problems with coping or mood swings, (8) relationships with other people, (9) daily activities, (10) sex life, (11) the impact of the disease or its treatment on appearance, (12) the intensity of the impact of the disease on the subject in general. All quality-of-life questions will cover the last 4 weeks prior to the survey. The respondents must choose 1 of 5 answer categories: (1) not at all, (2) a little, (3) average, (4) quite a lot, (5) very much. In the question regarding difficulties in performing duties at work, the authors added an additional category—“I do not work” [38]. The score ranges from 0 to 100, with higher scores indicating a poorer quality of life.

### 3.8. Nutritional Status

Body weight will be measured with the subject in a standing position with an electronic digital scale. The examined person will be weighed in her underwear without shoes, and the scores will be read out with an accuracy of 100 g [46].

Body height will be measured with a medical scale with a built-in height gauge with the subject in the standing anthropometric position (lower limbs straightened, feet set parallel to each other, upper limbs straightened, hanging loosely along the trunk, head set in the eye–ear plane). The individual will have her shoes and socks off, as well as hair ornaments. The measurement will be taken from the top of the head to the base on which the person is standing. Measurements will be read out with an accuracy of 1 mm [46].

Waist circumference will be measured at the midpoint between the lower margin of the least palpable rib and the top of the iliac crest, with the subject in a standing position with body weight evenly distributed between both feet, after emptying the bladder and with relaxed muscles, with an accuracy of 1 mm [47]. Hip circumference will be measured at the widest part of the buttocks, with the subject in a standing position with body weight evenly distributed between both feet, after emptying the bladder and with relaxed muscles, with an accuracy of 1 mm [47].

Based on anthropometric data, body mass index (BMI = weight (kg)/(height (m))^2^) [48], waist-to-hip ratio (WHR = waist circumference (cm)/hip circumference (cm)) [47], and waist-to-height ratio (WHtR = waist circumference (cm)/height (cm)) will be calculated [49]. Overweight will be defined as a BMI between 25.00 and 29.99 kg/m^2^, while obesity will be defined as a BMI ≥ 30.00 kg/m^2^. Central obesity will be defined as WHR > 0.8 [47] and/or WHtR ≥ 0.5 [50].

Body composition will be analyzed with the bioelectrical impedance (BIA) method using the body composition analyzer (ACCUNIQ BC-720). The measurement will be conducted with the subject in a standing position. The individual will stand barefoot in her underwear, and the measurement will be taken at least 4 h after a meal and at least 12 h after intense physical activity. The tested person will avoid consuming caffeine-containing beverages (e.g., coffee, energy drinks), use the toilet before the measurement (defecation and urination), and remove jewelry and any metal elements (e.g., a belt). The body composition analyzer will provide data on muscle, total fat, visceral tissue, and water content in the body.

### 3.9. Blood Pressure

At least 30 min before the measurement, the patient should refrain from consuming coffee, smoking cigarettes, and taking other stimulants [51]. Peripheral pressure will be examined with the subject in a sitting position, after a minimum of 5 min of rest, with the ACCUNIQ BC-250. The patient will be in a sitting position with her back supported in a quiet room, with thermal comfort maintained. The arm on which the measurement is made should be free of constricting clothing, bent at the elbow, relaxed, and supported at the level of the patient’s heart [51].

### 3.10. Anti-TPO Titer Concentration

The anti-TPO titer will be determined in venous blood taken from a peripheral vein of the forearm by qualified personnel from the medical laboratory. The concentration will be determined by immunochemistry on the “Alinity i” laboratory instrument and compared to a reference value of <5.61 IU/mL.

The factors influencing the anti-TPO result are anti-streptavidin and anti-ruthenium antibodies. Therefore, the measurement will be omitted for these patients. Biotin is also a factor that interferes with the anti-TPO titer measurement. Therefore, patients taking biotin supplementation will be advised to take a minimal break the day before the examination [52].

### 3.11. Nutrition Education

Nutrition education is planned for 12 weeks, with 6 individual meetings spaced about 2 weeks apart. There will be a total of 6 h of education in the entire program. The form of meetings will be online or in person, depending on the patient’s preferences. At the beginning of the education intervention, the patient will be presented with an interpretation of her eating habits, the nutritional value of her diet, and her nutritional status. A personalized goal (e.g., weight loss in the case of a patient with obesity) that the patient should achieve will also be discussed and set. During the education intervention, the following issues, among others, will be discussed with all participants: nutritional recommendations and essential nutrients (role, sources in food) in Hashimoto’s thyroiditis; factors affecting iron bioavailability; glycemic index and glycemic load—application and importance; weight reduction assumptions; snacking—causes and tips on how to minimize the need to reach for snacks; mindful eating; “Healthy eating plate”—nutritional recommendations for the Polish population presenting the correct proportions of individual product groups in a daily diet [53]; interactions between levothyroxine and food; the importance of microbiota in HT; *Lactobacillus plantarum 299v*—impact on human health based on scientific research (mainly on the immune system, iron, intestinal symptoms, blood pressure); and myths and facts about nutrition in HT. In addition to the above-mentioned topics, participants will be able to receive answers to individual questions/concerns.

All educational materials will be prepared based on the scientific literature and standards by The Polish Society of Dietetics and the National Public Institute—National Institute of Hygiene. Each participant will receive educational materials and a sample menu depending on energy needs to illustrate how meals and portions should look. Throughout the entire study period, participants will have the possibility of consulting with a dietitian, who will also support the introduction of changes in eating habits depending on individual personalized needs.

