## 2. Study Aim and Hypothesis

The primary objective of the trial is to assess the effect of a dietary intervention with probiotic *Lp299v* supplementation on body weight and quality of life in female AIDH patients.

The secondary objective of the trial is to evaluate the effectiveness of individual personalized nutritional counseling on several key parameters among patients diagnosed with Hashimoto’s thyroiditis. The specific focus areas for assessment include food selection and diet quality, body composition, serum anti-TPO, and blood pressure.

The research hypotheses are as follows:-Individual personalized nutrition education aimed at improving food selection and diet quality may enhance nutritional status, anti-TPO parameters in the blood, and the overall quality of life in AIDH patients.-The *Lp299v* strain may augment the impact of the individual nutritional intervention, particularly in terms of improving the quality of life, body weight status, and anti-TPO parameters in the blood.

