### 3.3. Randomization and Blinding

Participants will be randomly allocated, according to a generated randomization list, to the experimental group (approximately *n* = 50) or the control group (approximately *n* = 50). The randomization list will be generated by a researcher who is not involved in the experiment. The study is designed as double-blinded, meaning that neither the participant nor the intervention conductor will be aware of which group is the experimental group (receiving *Lp299v*) and which is the control group (receiving placebo) until the end of the experiment. Each patient will be assigned a unique code number, which will be used to label all results to maintain blinding.

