### 3.12. Lactiplantibacillus plantarum 299v

The experimental group will take 1 × 10^10^ CFU (colony-forming units) of *Lactiplantibacillus plantarum 299v* contained in Sanprobi IBS^®^ once a day with a meal. The carrier will be potato starch and magnesium salts of fatty acids (capsule shell: hydroxypropyl methylcellulose). The control group will take a capsule with a placebo, i.e., granulated potato starch and magnesium stearate (capsule shell: hydroxypropyl methylcellulose), also once a day with a meal. At each educational meeting, participants will be asked whether they are taking the given capsules and whether they have experienced any side effects. After the intervention, participants will be asked about any missed doses of capsules. Throughout the study period, both the probiotics and the placebo will be stored in the refrigerator, following the manufacturer’s recommendations. *Lp299v,* contained in the preparation “Sanprobi IBS^®^”, is registered with the Chief Sanitary Inspector. In addition, the preparation received a positive evaluation from the Institute Of Monument Children’s Health Center (IPCZD) No. 5/DJW/2020 and the Quality Institute of the Jagiellonian Center of Innovation, which states that SANPROBI IBS ^®^ has good probiotic properties and is safe for the consumer. The manufacturer declares that the amount of the probiotic strain in CFU will remain consistent throughout the product’s shelf life.

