### Strengths and Limitations

This study has several strengths. The experiment will complement the knowledge about the impact of diet and probiotic supplementation on AIDH. Another strength is the form of education, which should be more understandable for patients, as opposed to giving dietary recommendations without explanation. In our study, we will assess whether changes in the consumption of the most important nutrients in Hashimoto’s (e.g., selenium, iodine, iron, zinc, magnesium) correlate with the change in anti-TPO, other nutritional parameters, and quality of life, which, to our knowledge, has not been investigated so far. Additionally, the effect of *Lp299v* on AIDH has not been explored, despite evidence of an immunological effect. Therefore, we will be the first to explore this area. Another strength is the length of the intervention. The mentioned studies show that 12 weeks of nutrition education brings health benefits and that only 6 weeks of *Lp299v* supplementation was enough to notice changes in inflammatory markers. It is worth emphasizing that the trial does not present any health risks to participants; the *Lactiplantibacillus plantarum 299v* used is a commercial dietary supplement (not a medical drug), and nutritional counseling aims to improve the diets of patients and is consistent with recommendations and nutritional standards.

The study limitations should also be mentioned. The first is the method of group selection, which is deliberate and snowballed. Second, the nutrient estimates from the Food Records Questionnaire are dependent on the patient’s conscientiousness and accuracy. Another limitation is that the collected data on the consumption and intake of the probiotic may be subject to error, as the researchers will rely on information provided by the patients. The authors, however, will provide detailed instructions for completing the food diary, as well as answering any questions that participants have when completing the surveys. Participants will be asked to answer the questions honestly and conscientiously. It should also be mentioned that meetings are planned every 2 weeks, which gives the opportunity to introduce changes. However, for some patients, weekly meetings are more motivating.

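### The health impact of the trial's own test strain is taught to both arms during the blinded 12 weeks, an avoidable risk to the only randomised contrast

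*Protocol article*

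**What the plan says.** Section 3.11 sets the timetable: "Nutrition education is planned for 12 weeks, with 6 individual meetings spaced about 2 weeks apart". It then says that "the following issues, among others, will be discussed with all participants". Two of the topics bear on the test product: the role of the microbiota in Hashimoto's thyroiditis, and the strain by name with its "impact on human health based on scientific research (mainly on the immune system, iron, intestinal symptoms, blood pressure".

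These sessions fall within the blinded period. Section 3.3 requires that "neither the participant nor the intervention conductor will be aware of which group is the experimental group" until the experiment ends.

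The primary objective in Section 2 concerns the effect of "supplementation on body weight and quality of life in female AIDH patients". Quality of life is self-reported on ThyPROpl (Section 3.7: "The respondents must choose 1 of 5 answer categories") over the preceding four weeks. Body weight is read from a scale (Section 3.8).

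Several statements bear on use of the strain outside the trial:
- Strengths and Limitations says that the product "used is a commercial dietary supplement (not a medical drug").
- Section 3.2 bars use of Lp299v, in the paragraph on exclusion criteria.
- Section 3.6 has all participants asked in general terms about medicines, supplements and herbs.
- Section 3.12 has a check at each educational meeting: "participants will be asked whether they are taking the given capsules and whether they have experienced any side effects".

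**The concern.** Both arms receive the same nutrition education, so capsule content is the only randomised difference. A dietitian who explains to placebo women what the test strain is reported to do gives them a reason to obtain it, and the strain name is enough to find it in the shops. Any such use makes the arms more alike. The same teaching may also raise expectations in both arms. A larger placebo response leaves less room for a difference in a questionnaire score.

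A third route is narrower. Intestinal symptoms are among the effects discussed, so a woman who notices a change, or notices none, might form a view of which capsule she has. If that happened, answers to ThyPROpl could differ between arms for reasons unrelated to the strain.

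The teaching is not needed for either hypothesis in Section 2. The education is meant to act through food selection and diet quality, and the strain is tested through the capsule.

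**Working it through.** **Reading the sections together**

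1. *Who is taught, and when.* Sections 3.11 and 3.3 together place strain-specific teaching in both arms while participants must remain blind. This is explicit in the text.
2. *Whether controls could take the strain.* The product is on the market. The bar on Lp299v stands with the eligibility criteria. The article attaches no check to it after entry.
3. *Whether such use would be seen.* The Section 3.12 question concerns the capsules supplied. The Section 3.6 question would cover a purchased supplement, and Section 3.4 says that all parameters are measured at baseline and at 12 weeks, so it may be asked again at the end. It is not described as repeated at each meeting.
4. *Direction of effect.* Control use and a higher placebo response both pull towards no difference. Differential reporting needs guessed allocation and could act the other way. It does not touch scale-measured weight.

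**Illustration of dilution**

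Inputs from the article: 47 per arm, 5% significance and 80% power (Section 3.2), two-tailed tests (Section 3.13). The article gives an expected 50% improvement in quality of life but no standard deviation, control value or control rate, so the figure of 47 can be neither reproduced nor refuted. A standardised effect of 0.5 would need 63 per arm two-sided, so 47 does not come from reading 50% in that way.

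The standardised effect that 47 per arm can detect, by the normal approximation, is

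d = (1.960 + 0.842) × √(2/47) = 2.802 × 0.2063 ≈ 0.578.

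An exact t-test calculation gives 0.584. This is solved back from the sample size and is an assumption here.

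Let c be the share of controls taking the strain (assumed), each gaining the full effect. The contrast becomes d(1 − c), and power ≈ Φ(2.802 × (1 − c) − 1.960). The number per arm that restores 80% is 47/(1 − c)², rounded up.

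| c | Φ argument | Power at 47 per arm | Per arm for 80% |
|---|---|---|---|
| 0 | 0.842 | 80% | 47 |
| 10% | 0.561 | 71% | 59 |
| 20% | 0.281 | 61% | 74 |
| 30% | 0.001 | 50% | 96 |

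The formula treats every such control as exposed for the whole 12 weeks. If late starters gained only half the effect, 20% uptake would act like c = 10%, with power of about 71%. The table is therefore close to a worst case for each uptake rate.

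**The case against.** A reader might infer that women are taught the strain's benefits and told which bowel changes to look for. The article does not say so. Section 3.11 speaks of impact as shown by research, and intestinal symptoms appear only as a topic. The Discussion's own review of the strain is mixed on blood pressure: it calls the effect ambiguous and cites one study in which systolic pressure rose. The route through guessed allocation is therefore possible but not documented.

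A reader might also infer that the primary outcome is biased. That goes too far. Capsules are identical, both sides are blinded and the teaching is the same in each arm, so raised expectation alone produces no difference between arms. Body weight is also unaffected by how women report.

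It would be wrong, too, to say that outside use goes unrecorded, because Section 3.6 asks about supplements. Other points soften the risk. Consent involves a detailed description of the study, so women probably know already that a probiotic is under test. Each is already taking a capsule that may contain the strain, which weakens the motive to buy it. Other probiotics are a lesser matter, since the Introduction says that results for one strain do not carry over to another. Rules on supplements during the trial may stand in the full protocol, and collecting an allocation guess is optional good practice.

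All of this limits the size and certainty of the problem. It does not give a reason to teach about the test strain during the blinded weeks. A dietitian presenting the strain's researched effects goes further than disclosure at consent.

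**Conclusion.** The point holds as a matter of avoidable risk. The article schedules strain-specific teaching for both arms during blinding, the product is on sale, and the check at each meeting would not pick up outside use. The expected consequence is a smaller contrast between arms and lost power.

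The power figures rest on three assumptions: the back-solved effect of about 0.58, the uptake rates, and full-duration use. The documents supply none of these. They also give no basis for sizing the rise in placebo response, or any bias from guessed allocation. No claim that blinding fails, or that the quality-of-life result will be biased, is supported. The change is worth making because it costs almost nothing.

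**What to change.** Move the Lp299v topic, and any probiotic-specific part of the microbiota topic, to a handout or session after the week-12 measurements. The rest of the education programme stays as it is.

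Add to the existing capsule question at each meeting one item on any probiotic product used outside the study, recording the strain. Wording it about probiotics in general avoids prompting interest in the named strain.

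Optionally, ask participants at week 12 which capsule they believe they received, so that the success of blinding can be described.

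The cost is a reordering of teaching material and one or two short questions. Sample size, visits and outcomes do not change. The downside is that participants receive the Lp299v information up to 12 weeks later.

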### 3.12. Lactiplantibacillus plantarum 299v

The experimental group will take 1 × 10^10^ CFU (colony-forming units) of *Lactiplantibacillus plantarum 299v* contained in Sanprobi IBS^®^ once a day with a meal. The carrier will be potato starch and magnesium salts of fatty acids (capsule shell: hydroxypropyl methylcellulose). The control group will take a capsule with a placebo, i.e., granulated potato starch and magnesium stearate (capsule shell: hydroxypropyl methylcellulose), also once a day with a meal. At each educational meeting, participants will be asked whether they are taking the given capsules and whether they have experienced any side effects. After the intervention, participants will be asked about any missed doses of capsules. Throughout the study period, both the probiotics and the placebo will be stored in the refrigerator, following the manufacturer’s recommendations. *Lp299v,* contained in the preparation “Sanprobi IBS^®^”, is registered with the Chief Sanitary Inspector. In addition, the preparation received a positive evaluation from the Institute Of Monument Children’s Health Center (IPCZD) No. 5/DJW/2020 and the Quality Institute of the Jagiellonian Center of Innovation, which states that SANPROBI IBS ^®^ has good probiotic properties and is safe for the consumer. The manufacturer declares that the amount of the probiotic strain in CFU will remain consistent throughout the product’s shelf life.

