## 3. Materials and Methods

### 3.1. Study Design and Ethical Approval

We plan a 12-week single-center, double-blind dietary intervention in which AIDH patients will be randomly allocated into two groups: experimental and control. Participants in the experimental group will receive individual personalized nutrition education along with the probiotic *Lactiplantibacillus plantarum 299v*, while in the control group, *Lp299v* will be replaced by a placebo. The form of the administered supplement (capsule) will be identical in both cases; neither the researcher nor the patient will have knowledge of its contents. The detailed schedule of the trial is presented in the following section. All visits for measurements and data collection will take place at the Dietetics Counselling Center, Department of Dietetics, Faculty of Human Nutrition, Warsaw University of Life Sciences. All tests performed during the intervention will be provided free of charge to the participants, who will not receive any financial benefits or cost reimbursements for participating in the study.

The study protocol was registered with and approved by the Ethics Committee for Research with Human Participation at the Institute of Human Nutrition Sciences, Warsaw University of Life Sciences, in compliance with the principles of ethics (Resolution No. 22/2021 and No. 21/2022). The study will adhere to the Declaration of Helsinki, and all participants will provide informed consent. Each participant will be presented with a detailed description, and any questions or concerns will be addressed. Participants will be informed that they may withdraw at any stage from the study without providing a reason. It is important to note that side effects of *Lactiplantibacillus plantarum 299v* are rare and do not pose a threat to the patient. To ensure participant retention, direct contact with the researcher will be available throughout the study period.

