### 3.4. Course of Intervention

The 12-week intervention will involve individual nutrition education for patients with Hashimoto’s thyroiditis conducted in two groups. One group will additionally receive the *Lp299v* strain (NE + *Lp299v* group), and the other will receive a placebo (NE + P group). Before the start of education, an assessment of dietary habits will be performed using a three-day food record questionnaire. Additionally, validated tools will be used to assess (1) the dietary habits and nutritional beliefs (FFQ-6 and KomPAN^®^ questionnaire [36,37]); (2) the quality of life with thyroid diseases (ThyPROpl) [38]; (3) physical activity level (Polish version of IPAQ questionnaire) [39]. Anthropometric measurements (body weight and height, waist and hip circumferences), body composition, peripheral arterial pressure, and anti-TPO blood concentration measurements will also be performed. All parameters will be measured twice: at baseline and after 12 weeks of the intervention to evaluate changes and (if possible) compare the measurements to reference values. A diagram of the study is presented below (Figure 1).

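### The side-effect question is stated only for the six meetings and the missed-capsule question only for the end, so up to about 2 of the 12 weeks may have no planned side-effect question and missed doses rest on one long recall

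*Protocol article*

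**What the plan says.** Section 3.12 assigns two capsule questions to two different times. During the programme: "At each educational meeting, participants will be asked whether they are taking the given capsules and whether they have experienced any side effects". At the end: "After the intervention, participants will be asked about any missed doses of capsules".

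The meetings are set out in section 3.11: "Nutrition education is planned for 12 weeks, with 6 individual meetings spaced about 2 weeks apart". The week of each meeting is not given. The same section places the feedback on baseline diet and the goal-setting at the start: "At the beginning of the education intervention, the patient will be presented with an interpretation of her eating habits". The legend of Figure 1 also gives one consultation every two weeks.

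Section 3.4 gives the length of the intervention as 12 weeks and says of the assessments: "All parameters will be measured twice: at baseline and after 12 weeks of the intervention". The items listed there are questionnaires, a food record and physical and blood measurements. A side-effect question is not among them.

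On leaving the study, section 3.1 states: "Participants will be informed that they may withdraw at any stage from the study without providing a reason". Sections 3.1 and 3.11 also keep a line to the researcher and to a dietitian open throughout.

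**The concern.** The side-effect question follows the education calendar, while capsule exposure follows the 12-week intervention. The two need not end together. If the last meeting falls before the last capsule, the contact that follows is, as described, about missed doses and not about symptoms. A woman who stops between meetings has no further meeting at which she would be asked.

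The missed-dose count has the reverse problem. Participants are seen about every two weeks, yet the count is taken once, at the end, over the whole period.

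What is at stake is the tolerability comparison of Lp299v with placebo and the description of exposure. Section 3.1 calls side effects rare, and the strengths and limitations section says that the trial presents no health risks. A blinded placebo comparison could supply data on this in a disease where, by the article's own account, probiotic trials are few. The same section concedes that data on probiotic intake may be in error because they depend on what patients report.

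**Working it through.** The plan states no figure for side-effect coverage, so there is none to reproduce. The check is schedule arithmetic.

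**Inputs**
- Intervention length: 12 weeks (sections 3.1 and 3.4).
- Meetings: 6, about 2 weeks apart (section 3.11).
- Capsules: one a day (section 3.12).
- Arm size: about 50 (section 3.3).
- Sample size: 100 enrolled, 47 per group needed (section 3.2).
- Week of the first meeting: not stated. Assumed to be week 0, with a range of week 0 to week 2.

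**Span of the meetings**

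Span = (number of meetings − 1) × gap = (6 − 1) × 2 = 10 weeks.

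**Time after the last meeting**

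Tail = 12 − (week of first meeting + span).

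| First meeting | Gap (weeks) | Last meeting | Tail (weeks) |
|---|---|---|---|
| Week 0 | 2 | Week 10 | 2 |
| Week 1 | 2 | Week 11 | 1 |
| Week 2 | 2 | Week 12 | 0 |
| Week 0 | 2.25 | Week 11.25 | 0.75 |
| Week 0 | 2.4 | Week 12 | 0 |

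The tail therefore runs from 0 to 2 weeks at the stated spacing or slightly wider. The week-0 row fits the text best. Education is to last 12 weeks and to open with feedback on the baseline diet, and a first meeting at week 2 would leave the first two weeks without education.

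**Size on the week-0 reading**
- Share of exposure: 2 / 12 = 17%.
- Per arm: 50 × 2 = 100 of 50 × 12 = 600 person-weeks.
- On the week-1 reading this halves to 50 of 600; on the week-2 reading it is 0.

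**Withdrawals**

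The plan allows for 100 − 2 × 47 = 6 withdrawals. For each, the period without a planned question runs from the last attended meeting to the day she stops, so normally at most about one two-week interval.

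**Missed doses**

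One recall covers up to 12 × 7 = 84 capsules. A count at each meeting would cover about 2 × 7 = 14.

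**After the fix**

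A side-effect question at the post-intervention contact brings the tail to 0 weeks in every row of the table.

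**The case against.** The strongest reply is that the two-week tail is inferred. No meeting week is fixed, nor is the day of the first capsule relative to the first meeting. Meetings at weeks 2 to 12, or slightly wider spacing, fit the wording and leave no tail. Feedback on the baseline diet also needs a returned and analysed food record, so the first meeting may come some time after baseline. This stands, and it is why the result is given as a range.

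Second, this is a journal article. Exit forms, severity grading or a fuller end-of-study questionnaire may sit in the full protocol. This stands for those details, and their absence is not part of the point. It is weaker for the timing of the two questions, because section 3.12 sets each one explicitly and describes the end contact as a missed-dose question.

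Third, a reader might infer more than the text supports:
- *That the last weeks and the women who withdraw are never covered.* Women who withdraw are asked at every meeting they attend, and contact with the researcher and dietitian stays open. Spontaneous reports are possible; they are just not solicited.
- *That adherence rests on a single recall.* Whether capsules are being taken is asked at each meeting. Only the count of missed doses is taken once.
- *That answers are coloured because participants are told side effects are rare.* Section 3.1 says this to the article's reader. It does not say that participants are told.
- *That any harm difference is biased towards none.* Both arms share the same schedule, and no difference in withdrawal between arms is documented. Such a bias is possible but not shown.

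**Conclusion.** The point holds in a limited form. As stated, side effects are asked about at the six meetings and missed doses once after the intervention. If the first meeting opens the education, up to about 2 of 12 weeks (17%; range 0 to 2 weeks) have no planned side-effect question. Events after a withdrawing woman's last attended meeting depend on her reporting them unprompted. The number of missed capsules rests on one recall over up to 84 doses.

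This assumes a first meeting at or near week 0, spacing of about two weeks, and capsules taken for the full 12 weeks.

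Importance is low. Section 2 lists no safety objective, and no primary or secondary endpoint changes. The reason to act is that the change is nearly free and reduces an error in the intake data that the authors themselves acknowledge.

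**What to change.** In section 3.12:
1. Ask the side-effect question also at the existing post-intervention (week-12) contact and, where a woman agrees, when she withdraws.
2. At every meeting and at week 12, record the number of capsules missed since the last contact, not only once at the end.
3. Report side effects and missed capsules by arm.

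Stating the planned week of each meeting in section 3.11 would also remove the ambiguity about the tail.

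The cost is a short change to one paragraph and a few minutes per contact. Women who complete the study need no extra visit. The exit question is voluntary, so the right to leave without giving a reason is kept. More events may be reported, in both arms.
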